### Integral movement therapy

Load and intensity of exercises will be increased according to participants’ abilities. Modifications of exercises are made by different body positions with decreasing the stability of the body position or increasing the elastic resistance. When a participant is able to perform a certain number of repetitions and sets of the required exercise without any compensatory movements, he/she can proceed to the next level of exercise. There will be 1–2-min breaks between each exercise and 20-s breaks between sets of the same exercise. In the set break, participants will perform easy trunk motions (e.g. hip circling, lateral flexion) to increase hydration of the intervertebral discs.

Protocol consists of four basic exercises, which are progressed through sessions (Additional file 4, part 2):Proprioception – sitting on an unstable surface – Swiss ball, with additional tasks with legs and arms.Strength – pushing task in different body positions:unstable position – from single-plane to multi-plane arm movements;stable position – high number of repetitions – single-plane movement.Strength – pulling task in different body positions:unstable position – from single plane to multi-plane arm movements;stable position – high number of repetitions – single-plane movement.Lifting and carrying loads:stoop lifting;squat lifting;half kneeling lifting.

### Local movement therapy

Loads and intensity of exercises will be increased according to participants’ abilities. Modifications of exercises are made through different body positions or increasing the load. When a participant is able to perform a certain number of repetitions and sets of a required exercise, without any compensatory movements, he/she can proceed to the next level of exercise. Breaks between exercises and sets are the same as in the integral movement therapy protocol.

Protocol consists of four basic exercises, which are progressed through sessions (Additional file 4, part 3):Abdomen curl.Trunk extension on roman chair.Hip bridge.Side plank.

## Outcome measures

### Primary outcome measures

There are two aspects of primary outcome measures. The first part of the measures is based on different questionnaires: level of disability (ODI questionnaire); physical activity (IPAQ questionnaire); and pain (NRS questionnaire). All questionnaires will be conducted at baseline, immediately after the intervention, and six months and 12 months after finishing the intervention, as medium- and long-term follow-ups. The second part consists of different functional tests: timed up and go test (TUG); sit to stand test; chair seat and reach test (CSR); 6-min walk test (6MWT); Biering Sorensen test (BS); modified Schober test (mSCH); and Sharpened Romberg balance test (SRB). Those will be collected at baseline and immediately after the intervention.

The ODI questionnaire is one of the instruments for measuring disability caused by LBP. The Slovenian version of the ODI questionnaire is a reliable and valid instrument for assessing outcomes of physical therapy in patients with chronic non-specific LBP [18]. IPAQ was developed as an instrument for cross-national monitoring of physical activity and inactivity and has reasonable measurement properties for monitoring population levels of physical activity among adults in diverse settings aged 18–65 years [19]. Pain intensity is frequently measured on an 11-point pain intensity numerical rating scale, where 0 means no pain and 10 is the worst possible pain. On average, a reduction of 2 points or a reduction of approximately 30% in the NRS is considered a clinically important difference [16, 20].

TUG test, sit to stand test, CSR and 6MWT are part of the Senior Fitness Test battery [21]. Specifically, the tests measure the level of physical abilities (strength, endurance, agility) that are impaired in patients with CLBP.

Weak trunk muscles and reduced flexibility/elasticity of the back and hamstrings were found as a residual sign, in particular among those with recurrence or persistence of LBP [22]. The BS test provides reliable measures of position-holding time and can discriminate between individuals with and without non-specific LBP [23]. Furthermore, the literature states that the mSCH test showed moderate validity and excellent reliability and metrically detected changes in sample of patients with LBP [24]. SRB has been reported to have good interrater reliability and test–retest reliability [25]. Balance will be measured in three different positions of feet—parallel, semi-tandem, and tandem positions—all with closed and opened eyes.

### Secondary outcome measures

Secondary outcomes include objective measures of trunk proprioception and strength. All of them will be performed as baseline and end-of intervention measures, respectively.

Trunk repositioning error test (REPerror) will be measured for trunk flexion movement. The participant will be led to a certain angle of trunk flexion with his/her eyes covered. He/she will try to remember and repeat the targeted position of the trunk on his/her own. Flexion angle will be measured on the level of TH12 with a digital goniometer (12–075, Baseline evaluation instruments®, ZDA). The result will be expressed in degrees and will represent the difference between targeted (first angle of flexion) and actual position. Everyone will perform three sets of two repetitions. The average of repositioning errors through all repetitions will be calculated and taken for further analysis.

Furthermore, a sitting balance test will be performed. Participants will try to sit as still as possible for 35 s on the balance board, which will be placed on the force plate. Software (Fitro sway, 3.1., Fitronic s.r.o., Bratislava, Slovakia) will collect the average changes in position of center of the pressure in the anteroposterior and lateral directions and the mean velocity (mm/s) of changes of position.

The maximal strength of trunk extensors, flexors, and lateral flexors will be measured under static conditions using a dynamometer (TNC, S2P Ltd., Ljubljana, Slovenia) with an embedded force sensor (PW10AC3–200 kg, HBM, Darmstadt, Germany) [26]. The individual will stand upright with feet shoulder width apart and arms across the chest. The pelvis will be tightly fixed against the rigid support with a strap. The upper support containing the sensor will be set at shoulder height. To acquire maximal voluntary contraction force (MVC), the individual will be asked to press against the upper support as strongly as possible for 3 s. Three MVC trials (with a 20-s pause between repetitions) will be acquired for pushing forward, backward, and aside (i.e. trunk flexion, extension, and lateral flexion). The strongest among the three MVC trials (mean force on 1-s time interval) will be used for further analysis.

## Data processing and statistical analyses

All data related to the study will be stored with the highest possible level of security. Questionnaire data, functional tests results, and exercise session diaries are typed into a database for subsequent transfer into SPSS for reporting and statistical analysis. All statistical analysis will be based on an intention-to-treat basis [27]. The investigator performing the analyses is blinded to treatment allocation. Data analysis will be performed using SPSS v19 (IBM Inc., Armonk, NY, USA).

The normality of distribution will be examined for all variables and those found to have a non-normal distribution will be properly transformed before further analyses. For primary and secondary outcome scores, the mean ± SD, median and range will be given for continuous data. Comparison of pre-intervention parameters of the two groups will be determined using two sample unpaired t-test. Differences between groups in the categorical outcome variable (IPAQ) at each time point (baseline, after treatment, and six-month and 12-month follow-ups) will be analyzed using the χ^2^ test and odds ratio. Analysis of variance with repeated measures will be used to identify changes of the functional outcome variables between baseline and after therapy.

For all tests, a *P* value < 0.05 will be considered significant. The minimal clinically important differences within and between groups comparisons are defined as ≥ 30%.

There will be no interim analyses. Only the authors of the protocol and study designers, SP and NŠ, will have access to all data during the intervention.

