### Sample size and sampling procedure

The sample size for this study is estimated based on clinically important improvements in patient measures through an anchor-based approach which was set at ≥ 30% [16]. In this regard, statistical power is considered to be 1-β (80%). Thus, the inclusion of at least 40 patients per group is planned [17]. Participants are allocated in a 1:1 ration to either of the two groups, local or integral, by a sealed envelope randomization system. Once the patient gives consent to enter a trial, an independent person will perform the randomization by picking one envelope out of 80, 40 of each option, and assigning the patient to the group written in the envelope.

Patients are blinded to treatment allocation, although they are informed about receiving exercise therapy without revealing the content of the treatment. Kinesiologists and physiotherapists who perform therapies are not blinded to treatment allocation, but they do not take part in the outcome measurements.

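### Baseline is significance-tested between randomised arms, but no outcome is analysed with its baseline as a covariate, which costs power on primary outcomes

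*Protocol article*

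**What the plan says.** All the methods at issue are in the protocol article, under Data processing and statistical analyses.

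- Baseline: "Comparison of pre-intervention parameters of the two groups will be determined using two sample unpaired t-test".
- IPAQ: "Differences between groups in the categorical outcome variable (IPAQ) at each time point", listed as baseline, after treatment, six months and 12 months, are analysed by a chi-square "test and odds ratio".
- Functional tests: "Analysis of variance with repeated measures will be used to identify changes of the functional outcome variables between baseline and after therapy".
- Threshold for every test: a P value below "0.05 will be considered significant".

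Under Primary outcome measures, IPAQ is listed with ODI, NRS and seven functional tests as primary. Baseline values exist for all of them: "All questionnaires will be conducted at baseline, immediately after the intervention, and six months and 12 months after finishing the intervention", and the functional tests are taken at baseline and directly after the intervention. No model with baseline as a covariate is named for any outcome.

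**The concern.** Allocation is by random draw of an envelope (Sample size and sampling procedure), so any baseline difference between arms is due to chance. A significance test of that difference asks a question whose answer is already known, and it does nothing to correct an imbalance. The baseline IPAQ chi-square is the same kind of test.

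The follow-up comparison of IPAQ ignores where each patient started. It also ignores the order of the categories if more than two are kept. The repeated-measures ANOVA does contain baseline, but its group-by-time term uses it by subtraction, which is less precise than regression on baseline. The section does not say which term of that ANOVA is the treatment comparison.

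With 80 patients and no stratification described, chance imbalance is a real prospect and precision is scarce. The measurements that would help are already being collected.

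**Working it through.** **1. The plan's own figure.** The article gives 40 per group at 80% power for an improvement of at least 30%. It states no SD, control rate, sidedness or named outcome, so 40 cannot be derived from its inputs. For a two-sided 0.05 comparison of two means, 40 per arm at 80% power corresponds to a standardised difference of √[2(1.960 + 0.842)²/40] = 0.626.

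**2. Inputs for the comparison of methods.** From the article: 40 per arm, 1:1 allocation, alpha 0.05. Assumed: two-sided testing; a standardised mean difference (SMD) of 0.5; a baseline to follow-up correlation r from 0.3 to 0.8; equal SDs at both times.

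**3. Formulas.** With the outcome SD set to 1:
- change score, which equals the group-by-time test of a two-time-point repeated-measures ANOVA: variance 2(1 − r)
- ANCOVA: variance 1 − r²
- ratio of ANCOVA to change score: (1 − r²)/[2(1 − r)] = (1 + r)/2, below 1 for every r < 1

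The effective difference is 0.5/√variance. Power is that of the two-sided t-test with non-centrality (effective difference) × √(40/2) and 78 degrees of freedom. The one further degree of freedom that ANCOVA spends is ignored.

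| r | variance, change | variance, ANCOVA | ratio | power, change | power, ANCOVA |
|---|---|---|---|---|---|
| 0.3 | 1.40 | 0.91 | 0.65 | 46% | 64% |
| 0.5 | 1.00 | 0.75 | 0.75 | 60% | 72% |
| 0.7 | 0.60 | 0.51 | 0.85 | 81% | 87% |
| 0.8 | 0.40 | 0.36 | 0.90 | 94% | 96% |

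At r = 0.3, for example, 0.5/√1.40 = 0.423 and 0.5/√0.91 = 0.524. The gain runs from 18 points down to 2.

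**4. The same at the difference of 0.626** (normal approximation). Change score v ANCOVA is 65.8% v 83.6% (r = 0.3), 80.0% v 89.9% (r = 0.5), 95.1% v 97.5% (r = 0.7) and 99.3% v 99.7% (r = 0.8).

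**5. If the group main effect were read as the treatment test.** It averages baseline and follow-up, so the difference halves to 0.313 and the variance is (1 + r)/2. Power is 41%, 37% and 33% at r = 0.3, 0.5 and 0.7. This is why group-by-time is called the best case above.

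**6. IPAQ.** The article does not state the categories. Assume three ordered categories at 30/40/30%, 40 per arm and a latent shift of 0.626 SD. Simulation with 400 runs per setting (Monte Carlo error about 2.5 points) gives:
- chi-square: about 60%
- proportional odds without baseline: about 70%
- proportional odds with baseline category: about 72% (latent r = 0.3), 78% (r = 0.5), 84% (r = 0.7)

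So about 10 points come from using the order. Baseline category adds roughly 2 to 14 more.

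**7. The interval for IPAQ.** In a simulation with the same categories and a latent shift of 0.5 SD, the median standard error of the log odds ratio rose from 0.428 unadjusted to 0.455 (r = 0.5) and 0.486 (r = 0.7) after adjustment. Odds ratios are non-collapsible: the adjusted estimate moves away from 1 and its standard error grows. Power can rise while the log-odds interval widens.

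**The case against.** The planned tests are valid. In a 20,000-run simulation the chi-square rejected in 5.1% of trials with no treatment effect. It can be said that this is a preference about efficiency, and that covariates belong in an analysis plan not shown here. The first part stands: validity is not in question. The second does not, because the article itself names the less efficient methods for IPAQ and for the functional tests.

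Some stronger readings are tempting, and the documents do not support them.

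- *Baseline is used only for testing.* A reader might infer this from the t-tests, but the repeated-measures ANOVA contains baseline for seven of the ten primary measures. If group-by-time is tested, chance differences at baseline are subtracted.
- *The IPAQ odds ratio is undefined.* That would follow only if more than two categories were kept without a common-odds model. The number of categories is not stated, and a two-category split makes the chi-square and odds ratio coherent and removes the point about order.
- *Adjustment narrows every interval.* It does so for continuous outcomes, but not for a log odds ratio (step 7).
- *Many baseline tests will mislead the trial.* With 21 independent tests the chance of at least one P < 0.05 is 1 − 0.95²¹ = 66%. That count needs sub-measures such as the six balance conditions to be taken separately, and independence is implausible for overlapping measures. No later analysis depends on a baseline test, so no treatment comparison changes.
- *ODI and NRS are shown to be analysed without adjustment.* The section names no between-arm model for their follow-up scores, so this cannot be shown either way.

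**Conclusion.** The point holds as a loss of efficiency, and it should be corrected. The baseline tests are uninformative under randomisation. IPAQ, a primary outcome, is compared without its baseline at each visit. For the functional tests the stated method is at best a change-score comparison, with ANCOVA variance equal to (1 + r)/2 of it.

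The direction does not depend on the assumptions, but the size does. At an assumed SMD of 0.5 and 40 per arm the gain is 18 points of power at r = 0.3, 12 at r = 0.5 (60% to 72%), 6 at r = 0.7 and 2 at r = 0.8, so it is minor where baseline and follow-up correlate strongly. The IPAQ gain, roughly 12 to 24 points over chi-square, rests further on three assumed categories and their assumed distribution.

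**What to change.** 1. Remove the baseline t-tests and the baseline IPAQ chi-square, and present baseline data by arm descriptively.
2. Analyse continuous outcomes measured once after baseline by ANCOVA, with the outcome's own baseline as covariate. For ODI and NRS, with three post-baseline visits, use a mixed model with arm, visit, arm-by-visit and baseline.
3. State how many IPAQ categories will be analysed. Use ordinal logistic regression, or binary logistic if dichotomised, over the three post-baseline visits with arm, visit, arm-by-visit and baseline category. Allow for repeated measurements within patient, and report the odds ratio with a 95% interval at each visit.

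The cost is revised wording and modest programming, with no new patients, visits or data. There are two small downsides. The proportional-odds assumption must be checked, with limited information at 40 per arm, and the adjusted odds ratio is a conditional one and should be described as such. Recruitment began in May 2018 (Trial status), so the change should be dated and fixed before any unblinded analysis.

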**Methods:**

The research design is a RCT with parallel-group design including two intervention groups: integral movement therapy and conventional local movement therapy. Participants in each group will receive 20 supervised sessions in a 10-week period, twice per week, for approximately 1 h per session. Outcome assessments will occur at baseline and immediately after intervention, follow-up will take place at six months and 12 months after the intervention. Prespecified analyses will evaluate the main effects of the treatment.

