## Participants

### Recruitment

Potential participants will be identified and recruited to the trial by general practitioners who work in the healthcare center in Kranj. Patients who seek medical help due to idiopathic CLBP which persists for at least 12 weeks [1] or had at least two acute episodes of LBP in the last 12 months and fulfill the inclusion and exclusion criteria will be referred to a responsible researcher. A researcher will approach the potential participant and inform them of all aspects of the study and provide a written information sheet, which will state that participation is voluntary and that they are free to withdraw at any time without affecting subsequent medical care (Additional file 3). Personal results and treatment summary will be available at the end of the trial to each participant on individual consultation.

There are no expected contraindications during the treatment protocol, except increased LBP, which can arise in some individuals. If so, according to a consultation with the medical doctor and executive researcher, the load and intensity of exercises will be decreased. If the pain exacerbates, the patient will discontinue the program.

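### No between-arm analysis is specified for the primary pain and disability scores at any visit after baseline, and the one model for continuous outcomes names no group-by-time term

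*Protocol article*

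**What the plan says.** All references are to the protocol article.

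- **Outcomes.** Primary outcome measures has two parts. The first is the questionnaires: "level of disability (ODI questionnaire); physical activity (IPAQ questionnaire); and pain (NRS questionnaire". Their timing is "All questionnaires will be conducted at baseline, immediately after the intervention, and six months and 12 months after finishing the intervention". The second is a set of physical performance tests, which the section calls functional tests, measured only at baseline and straight after the intervention.
- **Analyses.** Data processing and statistical analyses names three inferential procedures:
  - For baseline: "Comparison of pre-intervention parameters of the two groups will be determined using two sample unpaired t-test".
  - A chi-square test and odds ratio for "Differences between groups in the categorical outcome variable (IPAQ) at each time point", meaning all four visits.
  - For continuous outcomes after baseline: "Analysis of variance with repeated measures will be used to identify changes of the functional outcome variables between baseline and after therapy".
- **Analysis set.** The same section states: "All statistical analysis will be based on an intention-to-treat basis". It gives no rule for missing values.
- **Purpose.** Trial design and study setting describes a superiority trial with 1:1 allocation. Aims and research questions asks whether the integral programme does better than the local one on pain, quality of life and functional abilities. The abstract says: "Prespecified analyses will evaluate the main effects of the treatment".

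**The concern.** The statistical section goes into enough detail to assign a test to IPAQ visit by visit, yet assigns none to the two outcomes at the centre of a back-pain trial. If the section is followed as written, the superiority question for pain and disability is not tested, and their six- and 12-month values are described but not compared between arms. The visit, the model and the contrast could then be chosen after the data are seen.

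There is also a weakness in the one model that is named. It is aimed at change over time, and a change over time can be highly significant when the two programmes work equally well. Only a term that compares the arms answers the superiority question, and none is named.

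**Working it through.** **Step 1. Match outcomes to analyses.**

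| Outcome | Visits | Post-baseline analysis named |
|---|---|---|
| IPAQ | baseline, post, 6 and 12 months | chi-square and odds ratio at each visit |
| ODI | baseline, post, 6 and 12 months | none |
| NRS | baseline, post, 6 and 12 months | none |
| Functional tests | baseline, post | repeated-measures ANOVA of change, no group term named |
| Trunk strength, proprioception | baseline, post | none, unless functional is read broadly |

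The ANOVA's two time points are exactly the schedule of the functional tests, which supports the narrow reading. If ODI were nevertheless counted as functional, its six- and 12-month values would still lie outside the model, and NRS would still have no test.

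**Step 2. What a test of change shows.** A simulation of 5,000 trials gave both arms the same improvement of 0.6 SD, with 40 patients per arm and an assumed baseline-to-post correlation of 0.5. The change over time was significant in 99.9% of runs and the group-by-time term in 4.8%. The first result says nothing about which programme is better.

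**Step 3. The plan's own figure.** Sample size and sampling procedure gives 40 per group, 80% power and an improvement of at least 30%, but no SD, baseline mean or responder rates. The 40 therefore cannot be reproduced without assumptions. From the normal approximation, the standardized difference detectable with 40 per arm at two-sided 0.05 (sidedness is not stated) is

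d = (1.960 + 0.842) × √(2/40) = 0.626.

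The t distribution puts it slightly higher, at 0.634, which is used below.

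**Step 4. Group-by-time ANOVA against baseline adjustment.** Assumed inputs: d = 0.634 in units of the outcome SD, equal SDs at both visits, n = 40 per arm, two-sided alpha 0.05, baseline-to-post correlation r.

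- With two visits, the group-by-time test equals a t-test on change. SD of change = √(2(1 − r)), so the noncentrality is d/√(2(1 − r)) × √(40/2), on 78 degrees of freedom.
- ANCOVA on baseline: residual SD = √(1 − r²), so the noncentrality is d/√(1 − r²) × √(40/2), on 77 degrees of freedom.

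| r | SD, change | noncentrality | power | SD, ANCOVA | noncentrality | power |
|---|---|---|---|---|---|---|
| 0.3 | 1.183 | 2.396 | 66% | 0.954 | 2.972 | 84% |
| 0.5 | 1.000 | 2.835 | 80% | 0.866 | 3.274 | 90% |
| 0.7 | 0.775 | 3.660 | 95% | 0.714 | 3.970 | 98% |

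The variance ratio of ANCOVA to change is (1 − r²)/(2(1 − r)) = (1 + r)/2, which is 0.65, 0.75 and 0.85 at these correlations. Baseline adjustment is the more precise method for any r below 1.

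**The case against.** **Intent to compare is visible.** The statistical section sets a 30% threshold for comparisons within and between groups, and the design and Discussion commit to a superiority comparison. This stands as far as it goes: it would be wrong to say that the investigators will make no arm comparison. But a threshold is not a test, and none is assigned to ODI or NRS.

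**A condensed article may leave this to a fuller document.** That would excuse silence. Here the section does allocate tests, by outcome and by visit, and the allocation does not fit the article's own list of primary outcomes.

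**Change within the programme is a stated aim.** Aims and research questions puts the effect of the integral programme first and the comparison with local therapy second, so a test of change serves a stated question, and group-by-time is an ordinary term of a two-arm repeated-measures ANOVA. This stands. The criticism is that the term is not named, not that it is excluded.

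**Stronger readings that the article does not support.**

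- From "Prespecified analyses will evaluate the main effects of the treatment" a reader might infer that the arm main effect of the ANOVA will be the test, at a heavy loss of power. That sentence is general abstract prose, and the statistical section does not choose that term.
- A reader might infer that patients with missing visits will be dropped, because classical repeated-measures ANOVA usually uses complete cases. The article states intention-to-treat and gives no exclusion rule. The two-visit ANOVA cannot lose anyone for missing six or 12 months.
- "If the pain exacerbates, the patient will discontinue the program" concerns stopping the programme. It does not say that outcomes go uncollected, and no dropout rate is given. Any figure for bias from selective loss would be assumed, and where loss depends on unseen outcomes a mixed model would not remove most of it.

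**The exact form of the model is a preference.** True in part: any pre-named arm-by-visit analysis would close the gap. Baseline adjustment is preferred for the gain shown above.

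**Conclusion.** The point holds in this form: no between-arm analysis is specified for the primary ODI and NRS scores after the intervention, at six months or at 12 months, and the one post-baseline model for continuous outcomes is aimed at change with no group-by-time term named. This follows from the text alone and needs no assumption. For pain and disability in a superiority trial, it has to be settled before the data are analysed.

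The size of the gain from the better method does rest on assumptions: d = 0.634, equal SDs, 40 analysed per arm and a two-sided 5% test. Power is then higher with baseline adjustment by about 18, 10 and 3 percentage points (84 − 66, 90 − 80, 98 − 95) at correlations of 0.3, 0.5 and 0.7. These figures compare one post-baseline visit. The article does not support a finding that patients are dropped or that the arm main effect is the planned test.

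**What to change.** 1. **ODI and NRS.** Specify a linear mixed model with all post-baseline visits as outcomes, the baseline value as covariate, and arm, visit and arm-by-visit terms. Name one visit's arm difference in advance as the primary contrast, and take the other visits' contrasts from the same model.
2. **Functional and secondary outcomes measured once after baseline.** Replace the repeated-measures ANOVA with ANCOVA on the baseline value and test the arm effect. Within-arm change can still be reported descriptively for the first research question.
3. **Support for intention-to-treat.** State that outcomes continue to be collected at the scheduled visits from patients who stop the programme. Add a sensitivity analysis that assumes worse outcomes for patients who are missing after stopping because of pain. The mixed model alone does not deal with loss that depends on unseen outcomes.

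The cost is a change of wording, slightly more analysis in SPSS, which is already in use, and modest effort to follow programme-stoppers at visits already planned. No new measurement and no larger sample is needed.
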